## Method

### Study setting and recruitment

The main recruitment centers are located in Berlin, Leipzig, and Bayreuth, and are directed in accordance with the Medical School Berlin, the Federal Association of Bereaved Parents and Grieving Siblings in Germany (VEID e.V.), and the Association for Relatives to Suicide (AGUS e.V.). In addition, we will recruit participants through the study website (www.hilfe-nach-suizid.de) and advertisements in social media (e.g. social media platforms, self-help forums, specific websites for bereaved people), newspaper articles, flyers for self-help groups, and churches.

### Participants and eligibility criteria

All participants who meet the following criteria will be included in the study: (1) aged between 18 and 75 years, (2) experienced the loss of a close person through suicide, (3) have access to the Internet, (4) have sufficient German language skills, and (5) provide a signed consent form (Additional file 2). Participants with any of the following criteria will be excluded from the study: (1) acute suicidality, (2) elevated depression (defined by a score > 35 on the Beck Depression Inventory-II ), (3) bipolar disorder, (4) current psychotic experience, (5) elevated alcohol, drug, or substance use, (6) suspected borderline personality disorder (BPD), or (7) self-injurious behavior. The group intervention will be conducted by two group leaders: (1) an approved psychotherapist or a trainee in psychotherapy in the last phase of the training and (2) a group leader of a face-to-face self-help group for suicide bereavement.

### Sample size

We based the power and sample size estimations in the current study on results from previous studies examining the effectiveness of online bereavement interventions [34]. Assuming a between-subject effect size of *d* = 0.80, power of 0.80, alpha of 0.05 (two-sided), and a dropout rate of 30%, the within-group sample size should be at least 52 participants. Hence, we aim to include 104 participants in total.

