### Randomization

We will use block randomization without extra stratification: As soon as 10 participants are included, they are considered to form a group. A researcher (first author) who is not involved in participant recruitment, clinical assessments, or treatment, obtains the information by e-mail that a new group is complete. Then, the whole group is randomly assigned to either the treatment or the waitlist control group. The researcher then executes the randomization using a generated list at www.random.org. The person who is allocating the participants thus has no influence on the randomization and enrollment process. Following randomization, participants will be notified of their allocation.

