## Discussion

The primary aim of the study is to reduce suicidality and depression in people bereaved by suicide, using an online-group intervention. Furthermore, the intervention aims to reduce secondary parameters such as prolonged grief, anxiety, or PTSD. Last but not least, we are also interested in sociodemographic predictors (e.g. age, sex, relationship to the deceased) that predict successful treatment and in the cognitive processes (e.g. experience of stigmatization, guilt) that influence the participants’ general psychopathology.

People bereaved by suicide have a high risk of developing mental illnesses and committing suicide themselves [10]. For this reason, it is important to provide adequate low-threshold support. One of the main advantages of the program is that it is easy to access and geographically independent. The attendance of the participants and the group leaders is possible without much technical knowledge and without any special equipment. Furthermore, participants can largely remain anonymous, which might decrease hesitation to seek professional help, as after suicide people often face stigmatization in their environment. The advantages mentioned above also apply to the group leaders. Further, the intervention offers the unique opportunity to meet other people after suicide bereavement, which reduces social isolation.

With a planned sample size of more than 70 participants, this trial is adequately powered for detecting a medium effect size for the comparison between the treatment and the waitlist group. Additionally, we explore multiple predictors of treatment-outcome moderator variables to define detailed processes of the effectiveness.

The study has multiple methodological strengths such as block randomization and the use of a standardized manual with precise procedures and instructions that are based on cognitive behavioral principles. The group leaders receive detailed training and regular supervision to ensure treatment fidelity. Because the intervention is led by a psychologist and a self-help counselor who has also experienced suicide loss, both perspectives are considered, thus complementing each other’s work. Last but not least, this study uses validated questionnaires and an additional clinical interview in the diagnostic process to make sure the participants meet the inclusion criteria.

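### The planned 52 per group cannot be reproduced from its stated inputs and shows no allowance for randomising whole groups, and the claim of adequate power for a medium effect is not supported

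*Protocol article*

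**What the plan says.** The Sample size section begins "Assuming a between-subject effect size of *d* = 0.80" and adds power of 0.80, two-sided alpha of 0.05 and 30% dropout. From these it concludes that "the within-group sample size should be at least 52 participants", and then: "Hence, we aim to include 104 participants in total". It gives no group size, intraclass correlation (ICC) or design effect.

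The Abstract calls the trial group-cluster randomised. The Randomization section says "As soon as 10 participants are included, they are considered to form a group", after which the whole group is allocated to one arm. The Statistical analysis section plans a multilevel analysis, a test of the ICC, and ANCOVA on baseline depression and suicidality.

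The Discussion says: "With a planned sample size of more than 70 participants, this trial is adequately powered for detecting a medium effect size", for the comparison of treatment with waiting list.

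**The concern.** There are three difficulties.

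1. The per-group number does not follow from the inputs printed beside it.
2. The calculation, as shown, is one for individually randomised participants, whereas the unit of randomisation is the online group.
3. The Discussion claims power for a medium effect, whereas planning used d = 0.80, conventionally a large effect.

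The third matters most to a reader of the results. If the trial finds no difference, the Discussion invites the conclusion that a medium effect has been ruled out. The second matters because the nominal 80% at d = 0.80 depends on the ICC and on a small number of groups, and the article gives no figure for either.

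**Working it through.** **Inputs from the Sample size section.** d = 0.80 (so SD = 1), power 0.80, two-sided alpha 0.05, dropout 30%. Allocation is 1:1 (Trial design).

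**Step 1: reproduce the plan's figure.**
- Normal approximation: n per arm = 2(1.960 + 0.842)²/0.80² = 24.5, so 25.
- Two-sample t-test: power is 79.1% at 25 per arm and 80.7% at 26, so 26 completers per arm.
- Dropout: 26/0.70 = 37.1, so 38 enrolled per arm (76 in total). Multiplying by 1.3 instead gives 34.
- The plan's 52 is not reached. Other settings also miss it: one-sided alpha gives 31, alpha 0.025 gives 45, 90% power gives 49, 95% power gives 61. Alpha 0.01 by the normal approximation gives 53, and alpha 0.025 with 90% power and the ×1.3 inflation gives 51 to 54. These come near 52 but contradict the stated inputs.

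**Step 2: where 52 might come from.** Two explanations fit, and the article supports neither.
- 52 = 2 × 26, a two-arm total of completers read as a per-arm number.
- 52 × 0.70 = 36.4 completers, and 36.4/26 = 1.40. That would be a design effect of 1 + (10 − 1) × ICC at ICC = 0.40/9 = 0.044.

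**Step 3: the medium-effect claim.** Medium is taken as d = 0.50; the article gives no number. Two-sample t-test, unadjusted, no clustering:

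| Situation | Completers per arm | Power at d = 0.50 | Power at d = 0.80 |
|---|---|---|---|
| 70 in total, no dropout | 35 | 54% | 91% |
| 104 in total less 30% | 36 | 55% | 92% |
| 104 in total, no dropout | 52 | 71% | 98% |

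At d = 0.50, 63 per arm gives 79.5% and 64 gives 80.1%. So 64 completers per arm are needed, and 64/0.70 = 91.4, that is 92 enrolled per arm.

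**Step 4: clustering, for illustration.** Assumptions: k = 5 groups of 10 per arm (100 enrolled), m = 10 × 0.70 = 7 completers per group, the same ICC in both arms, and 2k − 2 = 8 degrees of freedom. The variance of the difference in SD units is V = (2/k)[ICC + (1 − ICC)/m]. Power comes from the noncentral t distribution with noncentrality d/√V and critical value 2.306. For example, at ICC 0.05, V = 0.4 × (0.05 + 0.95/7) = 0.0743, and 0.80/√0.0743 = 2.94, giving 73%. With a baseline correlation r, V is multiplied by 1 − r².

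| ICC (assumed) | Power, d = 0.80 | Detectable d at 80% power | Power, d = 0.80, r = 0.5 | Power, d = 0.50 |
|---|---|---|---|---|
| 0 | 83% | 0.77 | 92% | 45% |
| 0.02 | 79% | 0.81 | 89% | 41% |
| 0.05 | 73% | 0.87 | 84% | 37% |
| 0.10 | 64% | 0.97 | 76% | 31% |

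The detectable d and the last column assume no baseline adjustment.

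**The case against.** **The error in 52 is on the safe side.** This stands for individual randomisation: 52 exceeds 38, and unclustered power at d = 0.80 is 92%. The weakness lies in the clustering and the medium-effect claim, not in the number being too small for its own inputs.

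**A reader might infer that a two-arm total was mislabelled and doubled.** The article does not say so, and an undeclared design effect of 1.40 fits equally well. Only the failure to reproduce 52 is established.

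**A reader might infer that 104 and more than 70 contradict each other.** They need not. 104 is more than 70, and 104 × 0.70 = 72.8, so the Discussion may mean completers. It does call the figure a planned sample size, so its meaning should be stated. On either meaning, unadjusted power at d = 0.50 is about 55%.

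**A reader might infer that 52 per arm, or 5.2 groups of 10, cannot be formed.** The section gives 52 as a minimum, and the description of the intervention makes 10 a maximum group size. Six groups per arm would meet both.

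**ANCOVA is planned, so the unadjusted percentages may be too low.** This stands in part. The article gives no baseline correlation and claims no gain from one. With r = 0.5 assumed, power at d = 0.80 rises to between 92% and 76%. Without clustering, 36 per arm would reach 80% at d = 0.50 if r were about 0.67, so it is too strong to say that a medium effect can never be detected. In the cluster model of the working, power at d = 0.50 with r = 0.7 is still only 73% at ICC 0 and 53% at ICC 0.10.

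**The cluster inputs are assumed.** This is correct. The ICC, five groups per arm and equal ICC in both arms are all assumptions. Waitlist participants have no group sessions before week 12, and the Randomization section describes nothing that guarantees five groups per arm. The cluster figures show sensitivity and are not estimates.

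**Conclusion.** The point holds in this form. From the stated inputs, 26 completers or 38 enrolled per arm are required, and 52 cannot be reproduced. No allowance for clustering is shown although whole groups are randomised. The claim of adequate power for a medium effect does not match planning at d = 0.80 and has no support in the article.

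The first two findings rest only on what the article states. The size of the third rests on reading medium as d = 0.50 and on an unadjusted analysis. On that basis the shortfall is large, with power of 54% to 71% before clustering is counted. Whether the trial keeps 80% at d = 0.80 depends on the ICC and the baseline correlation. Under the illustrative assumptions, power runs from 83% down to 64% without adjustment and from 92% down to 76% with r = 0.5.

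**What to change.** No additional enrolment is needed.

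- **One planned total.** Use 104, or the nearest whole number of groups (for example 10 groups of 10, which is 100), in both the Sample size section and the Discussion. Say whether the Discussion's figure means completers.
- **A derivation that matches the design.** Replace the present one with a calculation that includes group size, number of groups per arm, an ICC range and cluster-level degrees of freedom. State whether baseline adjustment is assumed and, if so, with what correlation. If 52 already contains a design effect, say so and give it. An unclustered 76 should not be printed as the requirement beside a plan made in groups.
- **Power as a range.** Report power at d = 0.80 and the detectable effect over the ICC range. The figures in the working are an illustration; the authors should use their own ICC and correlation assumptions.
- **The Discussion sentence.** Delete the claim of adequate power for a medium effect and state the detectable effect instead.

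The cost is rewording and a short recalculation. The downside is that the stated power becomes less favourable.

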### Procedure

The flow of participants through the study is depicted in Fig. 1. Participants who are interested in the treatment can obtain general information about the program on the study website (www.hilfe-nach-suizid.de). This website provides extensive information on relevant topics for people bereaved by suicide. In addition, visitors to the website receive further information on helpful services (e.g. psychotherapy, counseling) and recommendations of useful literature.

**Fig. 1 Fig1:**
[figure not shown]
Participant flow. De = demographics, T = transmission of the death news, P = psychopathology: major depression, bipolar disorder, manic episode, borderline personality disorder, posttraumatic disorder, alcohol or substance misuse, psychotic episode, D = depression, A = anxiety, Su = suicidality, C = cognitions; G = grief, St = stigmatization; SS = social support, E = Evaluation of the intervention

To take part in the online intervention, participants first have to register on the website. Afterwards they will receive comprehensive information about the process of the study and a consent form for participation. As soon as participants have signed the consent form and have returned it (e.g. email, fax, or by post) they are invited to an online survey, which contains several questionnaires for diagnostic purposes (Table 1). To further examine the inclusion and exclusion criteria, participants will take part in a clinical telephone interview. This interview tests for acute suicidality, severe depression, acute psychotic experiences, bipolar disorder, PTSD, and BPD. Participants who do not meet the inclusion criteria receive further information on psychotherapy, counseling or self-help groups. In the case of clearly elevated scores on the measurements, participants are debriefed and are advised to see a doctor or psychotherapist. If the interviewer finds evidence of acute suicidality, he or she engages in crisis management strategies [35] or will arrange another telephone meeting to monitor the process. There are no specific provisions for the post-trial care of participants. If participants require further support after post-trial measurements, they are recommended by the project coordinators to seek further psychosocial support.

**Table 1 Tab1:**
[figure not shown]
Schedule of enrollment, interventions, and assessments (SPIRIT Figure)

SCID-I = Structured Clinical Interview for DSM-IV Axis I; SCID-II = Structured Clinical Interview for DSM-IV Axis II; SDPD = Dutch Screening Device for Psychotic Disorder; SRAI = Suicide Risk Assessment Interview; SBQR = Suicide Behaviors Questionnaire Revised; PHQ-D = German Patient Health Questionnaire; BDI-II = Becks Depression Inventory-II; SkPTBS = Screening for complex PTSD; IES = Impact of Event Scale; PTCI = Posttraumatic Cognitions Inventory; ICG = Inventory of Complicated Grief; GEQ = Grief Experience Questionnaire; STOSASS = Stigma of Suicide and Suicide Survivor Scale; BSSI = Beck Scale for Suicide Ideation; H-Scales = H-Scales to Assess Hopelessness; ACSS-FAD = Revised Acquired Capability of Suicide Scale; BSSS = Berlin Social Support Scale; GQ-D = German Group Questionnaire

### Randomization

We will use block randomization without extra stratification: As soon as 10 participants are included, they are considered to form a group. A researcher (first author) who is not involved in participant recruitment, clinical assessments, or treatment, obtains the information by e-mail that a new group is complete. Then, the whole group is randomly assigned to either the treatment or the waitlist control group. The researcher then executes the randomization using a generated list at www.random.org. The person who is allocating the participants thus has no influence on the randomization and enrollment process. Following randomization, participants will be notified of their allocation.

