**Methods:**

The intervention was developed based on focus groups with the target group. The cognitive-behavioral 12-module webinar-based group intervention focuses on suicide bereavement-related themes such as feelings of guilt, stigmatization, meaning reconstruction and the relationship to the deceased. Further, the webinar includes testimonial videos and psychoeducation. The suicide survivors are randomized to the intervention or the waiting list in a group-cluster randomized controlled trial. Primary outcomes are suicidality (Beck Scale for Suicide Ideation) and depression (Beck Depression Inventory-II) and secondary outcomes are symptoms of prolonged grief disorder (Inventory of Complicated Grief-German Version ), posttraumatic stress disorder ( Revised Impact of Event Scale ), stigmatization (Stigma of Suicide and Suicide Survivor ) and posttraumatic cognitions (Posttraumatic Cognitions Inventory).

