### Trial design

This study is a randomized control group design with two groups of equal sample size: the treatment group and the waitlist control group. The treatment group will receive treatment through the online group intervention immediately after registration. As a result of the focus groups with suicide survivors, the waitlist control condition was selected as the only one acceptable to the suicide survivors involved. A control that would not receive the intervention after the waiting period could reduce the motivation to participate.

This intervention is based on cognitive behavioral principles (psychoeducation, cognitive restructuring, dealing with difficult emotions such as guilt, shame, suicidality) and will take place once a week over a course of 12 weeks in total. The waitlist control group will receive the same intervention 12 weeks after registration. Participants will be randomly assigned to either group using computer-generated block-randomization. The study protocol was written in accordance with Statement Standard Protocol Items: Recommendations for Interventional Trials (SPIRIT) 2013 [33]; for the SPIRIT Checklist see Additional file 1).

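### The block in the randomisation is the group of 10 allocated whole to one arm, so no stated rule secures the equal arms the protocol claims

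*Protocol article*

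**What the plan says.** The Trial design section states: "This study is a randomized control group design with two groups of equal sample size". It then gives the method, worded as if individuals were allocated: "Participants will be randomly assigned to either group using computer-generated block-randomization". The Methods paragraph of the abstract describes a different unit: "The suicide survivors are randomized to the intervention or the waiting list in a group-cluster randomized controlled trial".

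The Randomization section explains the procedure: "We will use block randomization without extra stratification: As soon as 10 participants are included, they are considered to form a group". Once a group is complete, a researcher outside recruitment, assessment and treatment is told by e-mail, and "the whole group is randomly assigned to either the treatment or the waitlist control group", using a list generated at a public website. The section gives no block length counted in groups, no fixed number of groups per arm and no other constraint on the list.

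The Sample size section sets a minimum of 52 per arm and concludes: "Hence, we aim to include 104 participants in total". The section on the online group intervention makes 10 the maximum group size. The Discussion says: "The study has multiple methodological strengths such as block randomization". Under Trial status, recruitment runs from October 2018 to about May 2020.

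**The concern.** Permuted-block randomisation equalises the arms because each block contains a fixed number of allocations to each arm. In the Randomization section the block is the ten people who will share a webinar, and all ten go to the same arm. That is cluster allocation. It has none of the balancing property that the Trial design section and the Discussion rely on.

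Two things are at stake. With only about ten randomised units, an unbalanced split is not rare, and it costs precision. Groups also fill one after another over 19 to 20 months, so a run of the same allocation could place one arm mostly in one part of the enrolment period. The Statistical analysis section names baseline depression and suicidality as covariates, but not enrolment time.

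The target also does not fit the unit. Neither 52 nor 104 is a multiple of 10, and the Randomization section forms a group at ten.

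**Working it through.** **The plan's own figure.** The inputs in the Sample size section are d = 0.80, power 0.80, two-sided alpha 0.05 and 30% dropout. The normal formula n = 2(z₀.₉₇₅ + z₀.₈₀)²/d² = 2(1.960 + 0.842)²/0.64 gives 25 per arm, and the t-based version gives 26. Dividing by 0.7 gives 36 or 38. The stated 52 is therefore not reproduced. That is a separate matter. Below, 52 is taken as the plan's stated minimum.

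**Fit of target to unit.** 52/10 = 5.2 groups per arm. 104/10 = 10.4 groups, that is, ten full groups and four people over. For both arms to reach 52 with full groups, each needs at least six groups:
- with 10 or 11 groups this is impossible;
- with 12 groups it needs a 6:6 split (60/60, total 120).

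**Chance of imbalance.** Assume ten groups, each drawn independently with probability 1/2. The split then follows Binomial(10, 0.5), with 2¹⁰ = 1024 equally likely sequences:
- 5:5: 252/1024 = 24.6%
- 6:4: 420/1024 = 41.0%
- 7:3 or worse: (240 + 112)/1024 = 352/1024 = 34.4%
- 8:2 or worse: 2(45 + 10 + 1)/1024 = 112/1024 = 10.9%

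Under the same assumption with 12 groups, 6:6 has probability 924/4096 = 22.6%.

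**Precision.** With equal group sizes, the variance of the difference in means is proportional to 1/k + 1/(10 − k). Relative to 5:5 this is 25/[k(10 − k)]: 25/24 = 1.04 at 6:4, 25/21 = 1.19 at 7:3 and 25/16 = 1.56 at 8:2.

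**Power.** With 30% dropout, each group of 10 leaves 7 completers. The table uses d = 0.80, two-sided alpha 0.05 and a noncentral t with noncentrality d√[n₁n₂/(n₁ + n₂)], treating participants as independent.

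| Split of 10 groups | Completers | Power |
|---|---|---|
| 5:5 | 35/35 | 0.910 |
| 6:4 | 42/28 | 0.898 |
| 7:3 | 49/21 | 0.856 |
| 8:2 | 56/14 | 0.752 |

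**Allowing for clustering.** The document gives no intraclass correlation, so a range is assumed. A group-level test has 10 − 2 = 8 degrees of freedom and design effect 1 + (7 − 1) × ICC:
- ICC 0.01: power 0.812 at 5:5 and 0.742 at 7:3
- ICC 0.05: power 0.730 at 5:5 and 0.656 at 7:3

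**The case against.** The strongest reply is that independent draws are assumed, not stated. The researcher works from a generated list, and that list could be a balanced permutation of groups. A journal article may leave such a constraint to the full protocol. This stands, and it makes the probabilities above conditional. It does not remove the point, because the article does more than omit a block length: it explains its block randomisation as forming a group and allocating it whole, and elsewhere claims the benefits of the usual method.

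A reader might infer that equal arms cannot be delivered, or that nothing balances the arms. The document supports neither. The figure of 52 is a minimum and 104 an aim. Ten is a ceiling on group size, so smaller groups can run. Twelve full groups could give 60/60, and even independent draws give 5:5 about a quarter of the time. What is missing is a stated rule, including a rule for randomising a group that has not reached ten.

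It is also fair to say that imbalance in numbers alone is a modest threat. Up to 7:3, individual-level power stays above 0.80. Most of the loss in the group-level figures comes from clustering and the small number of groups, not from the split. No seasonal effect or drift in recruitment is documented, so alignment of arm with calendar time is possible rather than shown.

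**Conclusion.** The point holds in this form. The procedure as written is cluster allocation of whole groups with no stated balancing rule. It does not secure the equal arms in the Trial design section, and it does not support the strength claimed in the Discussion. Exactly 52 per arm cannot be made from full groups of 10.

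The size depends on how the list was built. If ten groups are drawn independently, there is about a one in three chance of 7:3 or worse, with contrast variance at least 1.19 times that at 5:5. There is about a one in nine chance of 8:2 or worse, with variance at least 1.56 times and individual-level power at or below about 0.75. If the list is already a balanced permutation of groups, the risk to balance largely disappears, and what remains is the wording and the target. The power figures also assume d = 0.80, groups of exactly 10 and 30% dropout spread evenly over groups. This is worth correcting because the remedy is cheap. It does not by itself invalidate the trial.

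**What to change.** - **Allocation.** For all groups not yet allocated, use a list of permuted blocks of whole groups with randomly mixed block sizes, for example 2 and 4, held by the researcher outside recruitment. Choose blocks that add up to the number of groups still expected. Report how the list used so far was generated and the split it produced.
- **Target.** Restate it in whole groups consistent with the minimum of 52, for example 6 groups per arm (60/60, total 120). Alternatively, give a rule for randomising a smaller final group, or restate the per-arm figure. Five groups per arm gives 50, which is below the stated minimum unless that figure is revised.
- **Wording.** In Trial design and in the Discussion, describe the design as group-level (cluster) randomisation, in line with the abstract.

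The cost is a new list for the remaining groups and a few sentences. Recruitment began in October 2018 and this protocol version is dated October 2019, so it is a mid-trial change to be documented as such. Blocking the remaining groups cannot undo imbalance among those already allocated. Six groups per arm means 120 − 104 = 16 more participants. The last allocation in a block becomes partly predictable; mixed block sizes, and the existing rule that allocation follows completion of a group, limit this.
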